##### **4.4.2 Data Collection and Follow-up for Withdrawn Subjects**

In the event that a subject has withdrawn from the treatment phase of the study, the research team will attempt to obtain permission for data collection for the twelvemonth follow-up period.

## 5 Study Device

### 5.1 Description

The MagVenture TMS Therapy System will be used under the subject IDE. The device consists of a magnetic stimulator, MagPro X100 with MagOption (K173620), and two magnetic coils, one for MT determination, C-B70, a treatment coil the Cool-B70 A/P coil .

The product code is OBP, and the classification regulations number for the System is 21 CFR 882.5805. All components, except the coils, in the subject pre-sub have previously obtained FDA clearance (K173620).

The MagVenture TMS Therapy System is cleared for treatment of MDD in adult patients who have failed to receive satisfactory improvement from prior antidepressant medication in the current episode. The MagVenture TMS Therapy System is based on the use of intermittent theta burst stimulation, or iTBS. This novel TMS protocol delivers treatment in only 3 min and is based on a patterned TMS paradigm delivered to the Left-Dorsolateral prefrontal cortex (LDPFC) at 120% of resting motor threshold (MT). It consists of bursts of 3 pulses at 50 Hz, with bursts repeated at 5 Hz, in a duty cycle of 2s on, 8 s off, over 3 min 9 s, and a total of 600 pulses. Treatment is administered daily for 5 days per week, for 4-6 weeks.

In the subject pre-sub for an IDE the device will differ from the previously cleared protocol on three important parameters:

- The stimulation protocol,
- The intended use, and
- The MT and treatment coils, C-B70 and Cool-B70 A/P coils, respectively

The TMS therapy will be delivered on both the R- and L-DLPFC, and in this case, treatment will be administered 3 times daily for 10 days in total (5 days per week). The stimulation of the R-DLPFC consists of a continuous theta burst stimulation (cTBS), which has not previously been cleared by the FDA.

The intensity of the newly approved iTBS treatment for adult patients with MDD, is based on the use of an intensity of 120% of MT. However, due to the nature of the accelerated treatment paradigm as well as the age of the target population (ages 13-18 yrs), the intensity will be decreased to 80% MT.

The stimulation parameters proposed here are based on previously published clinical trial literature, showing that bilateral accelerated TBS is both feasible and safe in adult and adolescent patients.

The coil used under the subject IDE, is a coil designed specifically for the use in double-blind, sham-controlled trials. The coil contains both an active site (A) and a sham site (P). The active

site is identical to the previously cleared standard coil, Cool-B70 (K173620) in terms of magnetic field properties. The sham site has a significantly reduced magnetic field, which is less than 5% of that of the active site, enabling a sham stimulation. As the coil contains both an active and a sham site, it is possible to blind the operator as well, as the coil looks identical on both sites.

The keeping of the blind is dependent on the use of a dedicated coil for MT determination. We intend to use the C-B70 coil, which is identical in terms of magnetic properties to the Cool-B70 A/P coil, but is a lightweight, non-cooled coil.

## **Short description of stimulator and magnetic coils**

### **MagPro Family - Magnetic Stimulators (K173620):**

The MagPro family consists of several models based on the same hardware- and software platform. The models which can be used for the TBS protocol are:

- MagPro R30,
- MagPro R30 with MagOption
- MagPro X100
- MagPro X100 with MagOption

The MagPro stimulator is a computerized, electromechanical medical device that produces and delivers non-invasive, magnetic fields to induce electrical currents directed at regions of the cerebral cortex. The magnetic stimulator is connected to a transducer coil which transfers the magnetic stimulation to the cortex.

### **C-B70 Coil**

This coil is used for the determination of the Motor Threshold (MT) of the individual patient. An MT coil is necessary in order to keep the blind of both operator and patient. C-B70 coil has a butterfly type design with two loops of windings. The coil is equipped with a trigger button on the coil handle as well as an intensity wheel, which enable the use of the coil for MT determination. MT needs to be determined for both the right and left motor cortex, when performing bilateral stimulation. The coil is produced with a slightly bent surface. The geometry of the C-B70-coil winding provides an improved coupling of the transducers magnetic field to the brain tissue, thereby reducing the required intensity. The geometry and magnetic field properties are identical to that of the active side (A) of the treatment coil, Cool-B70 A/P.

As the coil is used for a short period and only for MT determination, liquid cooling is unnecessary as the risk of overheating is minimal. The temperature of the internal winding is monitored by a thermal sensor – and if the temperature exceeds 43°C/109°F the MagPro system automatically stops.

**Treatment coil, Cool-B70 A/P coil:**

This coil is used for both active treatment and sham treatment. The coil has an integrated sham-side that enables double-blind, sham-controlled trial designs, in which both patient and operator are blinded. The coil's active side is identical in terms of magnetic field properties to the C-B70 MT coil presented above, as well as the Cool-B70 standard coil, which is cleared for treatment with iTBS (K173620). The sham side (P) has a significantly reduced magnetic field strength that is less than 5% of that of the active side. The coil is seen in the picture to the right. The coil looks identical on both sides and the MagPro Stimulator will guide the operator as to how the coil should be oriented during treatment of a given patient. This way, the operator will be kept blind towards whether or not the patient receives active or sham treatment.

The Cool-B70 A/P coil is also substantially equivalent to the standard Cool-B70 coil in terms of design elements, such as the use of liquid cooling in order to maintain the coil cool during treatments. The temperature of the internal winding is monitored by a thermal sensor – and if the temperature exceeds 43°C/109°F the MagPro system automatically stops.

**Output waveform**

Theta Burst Stimulation (TBS) provides bursts of three individual stimuli at a rate of 50 Hz (i.e. 20 ms apart), repeated at 5 Hz (i.e. 200 ms between burst). This is called a Biphasic Burst with 3 pulses.

**Biphasic Burst (Theta Burst)**

The biphasic burst waveform is able to provide a powerful stimulation. Biphasic Burst should be selected with 5 pulses in each stimulation with very low IPI (Inter Pulse Interval). The biphasic burst mode can be used to define Theta Burst stimulations. The MagVenture TMS Therapy System has undergone verification testing to ensure that the intensity of individual stimuli is equal throughout the course of treatment. It has been demonstrated that at the relevant TBS intensities required in the treatment setting, the individual intensity of the three stimuli is equal and kept constant.

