| Subject Participation Duration | 13 months                                                                                                                                                                                                                                                                                                                                                                                                                                                                                                                                                                                                                                                                                                                                                                                                                                                                                                                                        |
| Study Interventions     | The proposed study will examine sequential bilateral accelerated theta burst stimulation (aTBS). Three sessions are administered daily for 10 days (5 days per week). During each session continuous theta burst stimulation (cTBS) in which 1800 pulses are delivered continuously over 120 seconds to the right dorsolateral prefrontal cortex (RDPFC) is administered first, followed by iTBS in which 1800 pulses are delivered in 2 second bursts, repeated every 10 seconds for 570 seconds (1800 pulses) to the left dorsolateral prefrontal cortex (LDPFC). The theta burst stimulation (TBS) parameters were adopted from prior work, with 3-pulse 50 Hz bursts given every 200 ms (at 5 Hz) with an intensity of 80% of active motor threshold. The comparison group will receive 3 daily sessions of bilateral sham TBS treatment for 10 days. Subjects in both groups will take part in a daily psychotherapeutic treatment program. |

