In 2018, [name] and colleagues published a case report describing a seizure in a teenager during iTBS. A 15 year-old, female patient with Schizophrenia was enrolled in a neurophysiological study arm meant to deliver 600 pulses of iTBS at 80% active MT. The subject had no prior or current treatment with psychotropic medications. Prior to iTBS a physical examination, electrocardiogram, electrolytes, complete blood count, liver function tests, renal function tests, thyroid function tests, and computed tomography of the brain were all normal. There was no personal history of head injury, seizures, or other neurological disorders. The family psychiatric and neurological history was normal. The authors described a seizure with limb muscle contractions, eye lid fluttering, jaw contraction, foamy saliva, and urinary incontinence. The subject regained consciousness after 1 minute but was disoriented for approximately 20 minutes. The authors highlighted that this was the first published seizure with TBS in a child or adolescent.

[name] and colleagues recently completed a therapeutic trial of TBS with one of the most aggressive protocols to date. This study enrolled twenty youth (ages 16-24) with major depressive disorder. The subjects received ten sessions of sequential, bilateral 5 Hz/50 Hz TBS. Each session included 1800 pulses of cTBS delivered to the RDPFC followed by 1800 pulses of iTBS delivered to the LDPFC prefrontal cortex alternately. All TBS sessions were delivered at 80% active MT. The order of iTBS and cTBS was randomized for each patient. Subjects

endorsed mild headaches and other mild adverse events. There were no seizures or serious adverse events. The authors highlighted promising, preliminary clinical effects.

Collectively this prior work suggests that TBS interventions have similar safety, tolerability, feasibility, and clinical effects in adolescents as compared to adults. Treatment with TBS may improve suicidal ideation in adolescents. Novel, aTBS protocols offer similar safety profiles and clinical effects in adults with depression as compared to standard TBS protocols. With further study, aTBS protocols could provide pragmatic advantages in the treatment of adolescents with suicidal ideation.

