### 3 Study Design

#### 3.1 General Design

This pilot study is a randomized, double-blind, sham-controlled trial of sequential bilateral aTBS in adolescents with depression and suicidal ideation (Figure 7). Three sessions are administered daily for 10 days (5 days per week). During each session, cTBS in which 1800 pulses are delivered continuously over 120 seconds to the right dorsolateral prefrontal cortex (RDPFC) is administered first, followed by iTBS in which 1800 pulses are delivered in 2 second bursts, repeated every 10 seconds for 570 seconds (1800 pulses) to the left dorsolateral prefrontal cortex (LDPFC). The TBS parameters were adopted from prior work, with 3-pulse 50 Hz bursts given every 200 ms (at 5 Hz) with an intensity of 80% of active MT. The comparison group will receive 3 daily session of bilateral sham TBS treatment for 10 days.

[figure not shown]

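### The stimulation dose text contradicts itself in three places: pulses per burst, iTBS pulse total against train time, and the motor-threshold basis recorded for the cited youth precedent.

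*Protocol*

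**What the plan says.** **Pulses per burst.** Section 5.1, under Output waveform, describes three stimuli at 50 Hz repeated at 5 Hz and adds: "This is called a Biphasic Burst with 3 pulses". The next paragraph, Biphasic Burst (Theta Burst), says "Biphasic Burst should be selected with 5 pulses in each stimulation with very low IPI (Inter Pulse Interval", then closes by reporting that "the individual intensity of the three stimuli is equal and kept constant". Section 3.1 gives the trial dose "with 3-pulse 50 Hz bursts given every 200 ms (at 5 Hz) with an intensity of 80% of active MT". The Study Summary and sections 1.1, 6 and 6.3 also give three-pulse bursts.

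**Pulses and time.** For the right side, section 3.1 states "cTBS in which 1800 pulses are delivered continuously over 120 seconds to the right dorsolateral prefrontal cortex (RDPFC". For the left side, the Study Summary describes iTBS in 2-second trains, "repeated every 10 seconds for 570 seconds (1800 pulses) to the left dorsolateral prefrontal cortex". Sections 1.1, 3.1, 6 and 6.3 repeat the same iTBS figures. The Study Summary and section 6.3 give the session as 11.5 minutes.

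**The precedent.** Section 1.4 says that the open-label youth study of sequential bilateral TBS (N=20) used the dosing proposed here and was well tolerated. Section 1.5.1 says of that study: "All TBS sessions were delivered at 80% active MT". Table 1 lists the same study at 80% of resting motor threshold.

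**The concern.** The stimulation is the intervention under test. An operator, a monitor or the DSMB can judge whether it was delivered as planned only against one set of settings, and here the settings disagree. The device paragraph is worded as something to select, and nothing marks it as not applying to this trial. The iTBS pulse total and its timing stand together in every full statement of the intervention, so the mismatch is repeated each time.

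The third conflict bears on the safety argument. Of the studies summarised in section 1.5.1, the youth study is the only one described with 1800 cTBS and 1800 iTBS pulses per session, and the protocol presents it as tolerability evidence for the proposed dose. If its intensity was set on resting rather than active threshold, it did not use the intensity that this trial states.

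**Working it through.** **Inputs.** Bursts at 5 Hz, three pulses per burst, cTBS for 120 s, and iTBS in 2-s trains every 10 s for 570 s with 1800 pulses (section 3.1). Five pulses per burst (section 5.1, Biphasic Burst). Cleared iTBS protocol: 600 pulses, 2 s on and 8 s off, 3 min 9 s (section 5.1). Course: 30 sessions (section 1.6).

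**1. cTBS: pulses = pulses per burst × 5 per second × 120 s.**
- Three per burst: 3 × 5 × 120 = 1800. The stated total is reproduced exactly.
- Five per burst: 5 × 5 × 120 = 3000, or 67% more.

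**2. iTBS: pulses = pulses per burst × 10 bursts per train × number of trains.**
- At three per burst a 2-s train holds 3 × 10 = 30 pulses, so 1800 pulses need 1800 / 30 = 60 trains.
- 570 s holds 570 / 10 = 57 cycles, giving 57 × 30 = 1710 pulses: 90 short, 5.0%.
- Allowing one more train to start at 570 s gives 58 × 30 = 1740 pulses: 60 short, 3.3%.
- Over 30 sessions the shortfall is 1800 to 2700 pulses.
- With five per burst, 57 or 58 trains give 2850 or 2900, so that setting does not rescue the 1800 either.

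**3. Time needed for 60 trains.**
- Exactly 10 s from train start to train start: 59 × 10 + 2 = 592 s.
- Off-time counted from the last pulse: ten bursts 0.2 s apart plus the 0.04 s inside the last burst last 9 × 0.2 + 0.04 = 1.84 s, so the cycle is 1.84 + 8 = 9.84 s. Check on the cleared protocol: 19 × 9.84 + 1.84 = 188.8 s, which matches 3 min 9 s; the 10-s formula gives 192 s. For 60 trains: 59 × 9.84 + 1.84 = 582.4 s.
- On the 9.84-s cycle, 58 trains end at 57 × 9.84 + 1.84 = 562.72 s and a 59th would end at 572.56 s. So 570 s again holds 58 trains, or 1740 pulses.

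**4. Session length.** The stated 11.5 minutes is (120 + 570) / 60 = 11.5. With 60 iTBS trains it would be (120 + 582.4) / 60 = 11.7 to (120 + 592) / 60 = 11.9 minutes.

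**5. Precedent.** No arithmetic applies.

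| Place | What it says of the youth study |
|---|---|
| Section 1.4 | Used the dosing proposed in this trial; well tolerated |
| Section 1.5.1 | 80% of active threshold |
| Table 1 | 80% of resting threshold |
| Section 3.1 (this trial, for comparison) | 80% of active threshold |

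The second and third rows cannot both be true. If Table 1 is right, the first row fails on intensity.

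**The case against.** **The five-pulse sentence looks like stray device text.** It sits in a description of the stimulator, the paragraph goes on to speak of three stimuli, and five pulses would break both stated totals. Section 5.3 refers administration to the user manual, and section 5.1 promises trial-specific instructions for use that are not shown. This stands as far as it goes. A reader might infer that participants will be given five-pulse bursts and 67% more cTBS pulses; the protocol does not support that. It supports only that one sentence conflicts with the rest.

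**The iTBS gap is small and may be rounding.** Three times 190 s is 570 s, so the duration may be a tripling of the cleared sequence of about three minutes. Tripling leaves out the two 8-s gaps between blocks: 3 × 188.8 + 2 × 8 = 582.4 s. That is a plausible source, but the protocol does not state it, and the timing as written still does not give 1800. The objection is right that cTBS is unaffected and that 5% is the upper end.

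**The threshold conflict concerns a cited study, not this trial.** That is correct. A reader might infer that this trial's own intensity is undefined between active and resting threshold, because section 5.1 follows a cleared protocol at 120% of resting threshold with "the intensity will be decreased to 80% MT", and because the threshold procedure written out in section 6.4 defines resting threshold. The protocol does not support that reading. Wherever it gives a type for this trial's treatment, the type is active; the Study Summary uses the short and full forms in the same entry; and the section 6.4 procedure is for biomarker testing on a different stimulator. The absence of a written procedure for the treatment threshold is missing detail, not a contradiction.

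**Conclusion.** The point holds in three limited parts.

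- **Burst setting:** one sentence in section 5.1 gives five pulses against three everywhere else. Five is incompatible with the stated cTBS total (3000 against 1800).
- **iTBS:** the stated timing gives 1710 to 1740 pulses against 1800. Set against the 3600 pulses stated for the whole session, the gap of 60 to 90 is 1.7% to 2.5%. Equally, the stated time is about 12 to 22 s short of what 60 trains need. The range depends on whether a train may start at 570 s and on how the 10-s cycle is measured; none of the conventions tried yields 1800 in 570 s with three-pulse bursts.
- **Precedent:** one of two entries for the same study is wrong, and the claim of earlier tolerability at this dose depends on which. The protocol gives no figure linking active to resting threshold, so no size is put on the difference.

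These are conflicts in the text. They do not show that any dose was wrongly delivered, and fit with a stated total does not by itself settle which figure is right.

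**What to change.** The sponsor should reconcile the Study Summary, sections 1.1, 3.1, 5.1, 6 and 6.3 into one dose specification giving pulses per burst, number and timing of trains, total pulses per side and session duration, and have the other sections refer to it. The five-pulse sentence should be reconciled with the Output waveform paragraph or marked as not describing this trial's setting.

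The entry for the youth study should be checked against its source and corrected in section 1.5.1 or in Table 1. The section 1.4 statement that it used the proposed dosing should then be kept or qualified to match. The unqualified threshold wording in the Study Summary and sections 4.3 and 5.1 can be aligned in the same edit.

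The cost is a text amendment with the usual submission. Design, sample size and analysis are untouched. If treatment has begun, the parameters that the study software stores (section 9.3, Data Management) allow the reconciled text to be checked against what was set. Which values are right is for the sponsor to establish.

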**Instructions for Use**

For your convenience we have submitted a copy of the Instructions for use (IFU) pertaining to The MagVenture TMS Therapy System that was cleared in August 2018, K173620. This is the standard iTBS 3 min protocol that the protocol in the present pre-sub builds on.

We have also submitted the IFU pertaining to the use of the Cool-B70 A/P coil.

Before submission of an IDE pertaining to this trial, a full IFU will be made available for this trial specifically.

### List of components

List of components (Table 2) that make up the system in this pre-sub along with the specific FDA submission numbers for each component that received a prior 510(k) clearance.

| Table 2 MagVenture TMS Therapy System Components |                            |                                                          |          |
|---------------------------------------------------------|----------------------------|----------------------------------------------------------|----------|
| Components                                       | Prior FDA clearance | Specific FDA 510(k) submission number             |          |
| R30, Stimulator                                         | Yes                        | K173620, K171481                                         | K150641, |
| X100, Stimulator                                        | Yes                        | K173620, K171481                                         | K150641, |
| X100 with MagOption, Stimulator                         | Yes                        | K173620, K171481                                         | K150641, |
| C-B70, coil                                             | No                         | Substantially equivalent to Cool-B70, cleared in K173620 |          |
| Cool-B70 A/P coil                                       | No                         | Substantially equivalent to Cool-B70, cleared in K173620 |          |
| Cooler Unit                                             | Yes                        | K173620, K171481                                         | K150641, |
| Trolley                                                 | Yes                        | K173620, K171481                                         | K150641, |
| Isolation Transformer                                   | Yes                        | K173620, K171481                                         | K150641, |
| Vacuum Pump and Pillow*                                 | Yes                        | K173620, K171481, K171967*                               | K150641, |

|                    |     |                                           |
|--------------------|-----|-------------------------------------------|
| Pillow case        | Yes | K173620, K150641,
K171481, K172667     |
| Super Flexible Arm | Yes | K173620, K150641,
K171481              |
| Treatment Chair    | Yes | K173620, K150641,
K171481,
K171967* |
| Cap                | Yes | K173620, K150641,
K171481, K172667     |
| Software v. 7.2    | Yes | K173620                                   |

